# Evaluating the efficacy of moving cupping for chronic low back pain using shear wave elastography: A parallel-arm, randomized controlled trial

**DOI:** 10.1097/MD.0000000000034067

**Published:** 2023-08-04

**Keywords:** chronic low back pain, complementary therapy, Korean medicine, moving cupping, muscle relaxation, noninvasive treatment, pain management, randomized controlled trial, shear wave elastography, ultrasonography

## Abstract

**Methods::**

We developed a randomized controlled trial (RCT) protocol for evaluating the effectiveness of a noninvasive treatment using moving cupping by assessing muscle relaxation with shear wave elastography (SWE). It involves the recruitment of 68 patients with CLBP and randomly assigns them to either the treatment or control group. The treatment group will receive moving cupping therapy for 2 weeks, while the control group will receive placebo treatment. It will utilize SWE to evaluate muscle relaxation at baseline, after 2 weeks of treatment, and 1 week after the end of treatment. Subjective reports of pain intensity and quality of life are also recorded at each time point.

**Discussion::**

The protocol developed here utilizes SWE to objectively measure muscle stiffness, and coupled with moving cupping therapy, may be effective in conveying relative comparisons before and after treatment. Moving cupping therapy is expected to promote muscle relaxation and pain relief in patients with CLBP. This study has the potential to contribute to the development of objective measures for evaluating the therapeutic effects of traditional therapies and to provide valuable insight into their efficacy.

## 1. Introduction

Chronic low back pain (CLBP) is a common condition that affects millions of people worldwide. It is defined as pain that persists for more than 3 months in the lower back region, and is one of the leading causes of disability and work absenteeism.^[1]^

Moving cupping is a traditional therapy that has been used for centuries to manage pain and promote relaxation. This therapy involves applying suction cups to the skin, which are subsequently moved around the body to promote blood flow and relieve muscle tension.^[2]^ Recently, moving cupping has gained popularity as a complementary therapy for managing CLBP owing to its noninvasive and cost-effective nature.^[3]^ It has been suggested that moving cupping may be particularly effective in treating CLBP by targeting muscle tension and improving circulation.^[4]^

One of the main challenges in evaluating the effectiveness of moving cupping for CLBP management is the lack of objective measures to assess its therapeutic effect. Although subjective reports of pain relief are commonly used to evaluate the efficacy of complementary therapies, they are often unreliable and may be influenced by placebo effects.^[5]^ Shear wave elastography (SWE) is a novel imaging technique that allows for the noninvasive assessment of muscle stiffness and relaxation. SWE provides a quantitative measure of muscle relaxation by measuring the speed of shear waves propagating through the muscle tissue, which can be used to evaluate the efficacy of moving cupping for CLBP management.^[6]^

The aim of this study was to develop a randomized controlled trial (RCT) protocol to evaluate the effectiveness of moving cupping for CLBP management using SWE to assess muscle relaxation. Specifically, it investigates whether moving cupping promotes muscle relaxation and alleviates pain in patients with CLBP. By providing objective measures of muscle relaxation and pain relief, this RCT protocol has the potential to significantly improve our understanding of the efficacy of moving cupping as a complementary therapy for CLBP. The findings may provide valuable insights for clinicians and researchers to optimize the clinical application of moving cupping and SWE for CLBP management, potentially improving patient outcomes and quality of life.

## 2. Methods

### 2.1. Ethics statements

Ethical approval for this study was obtained from the Pusan National University Medicine Hospital, National Clinical Research Center for Korean Medicine (PNUKHIRB-2022-12-002-001) on January 3, 2023. This clinical research protocol was based on the content registered and approved by the Clinical Research Information Service (http://cris.nih.go.kr) of the Republic of Korea (KCT0008282) on March 3, 2023.

### 2.2. Study design and population

This study aims to investigate the efficacy and safety of moving cupping therapy for chronic pain using a parallel-arm RCT. The target population will consist of patients with CLBP who have experienced pain for at least 12 weeks. The study will be conducted at the outpatient clinics of the Pusan National University Hospital and Korean Medicine Hospital.

To ensure blinding, the study will include only patients with CLBP who have no prior experience with moving cupping. The study will be conducted by independent practitioners, with one performing the moving cupping treatment and the other evaluating SWE independently. Each treatment will be administered 4 times (twice a week, for 2 weeks), and a follow-up evaluation will be conducted 1 week later.

This study was designed as a superiority trial with a level of significance set at α = 0.05, a type II error (β) of 0.2, and a power of the test of 80%. The sample size was calculated based on similar studies,^[7]^ with a 1:1 ratio between the intervention and control groups, and a dropout rate of 15% was considered in each group. Sixty-eight patients with CLBP will be randomly assigned to either the intervention or control group in sealed envelopes. After treatment, patients will undergo an evaluation.

#### 2.2.1. Participant recruitment.

Participants will be recruited according to a plan approved by the Institutional Review Board and the Clinical Research Information Service at Pusan National University Medicine Hospital, National Clinical Research Center for Korean Medicine. The study will be explained to the participants by their primary physicians and written informed consent will be obtained from those who choose to participate.

#### 2.2.2. Inclusion criteria.

Individuals aged 18 years or older but under 60 years of age.^[8]^Individuals with symptoms of low back pain lasting for at least 12 weeks.^[9]^Individuals with a body mass index (BMI) of <35 kg/m^2^.^[10]^Individuals with a numeric rating scale (NRS) pain intensity score ≥4.^[11]^Individuals who can understand the purpose and procedures of the study, and voluntarily decide to participate and provide written consent after receiving an explanation.

#### 2.2.3. Exclusion criteria.

Individuals with medical experience of moving cupping.QIndividuals with medical experience of gold thread therapy.^[12]^Individuals diagnosed with spinal tumors, spinal infections, or ankylosing spondylitis.Individuals with a history of spinal surgery such as spinal fusion or laminectomy.Individuals with factors that may affect hemostasis such as taking anticoagulants or antiplatelet agents, or having bleeding disorders.Individuals with severe atopic dermatitis, keloid-prone skin, other skin hypersensitivities, or uncontrolled diabetic skin diseases.Individuals with a substantial neuropsychiatric history or current neuropsychiatric disorders.Individuals with a history of alcohol or substance abuse.Pregnant or lactating women or women planning to become pregnant.

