### 2.3. Intervention

#### 2.3.1. Moving cupping.

During the intervention, the participants will assume a prone position on a plinth with both elbows flexed to 90° and their shoulders abducted to 120° with external rotation. Cushions will be placed under the pelvis and legs to increase comfort, reduce lumbar lordosis, and optimize transducer contact, thereby enhancing the accuracy of the measurements obtained during the intervention.^[13]^ Thereafter, moving cupping will be administered bilaterally at the L1-5 level spinous process, 4 to 8 cm from the midline, for 5 minutes on each side, with pressure between 18 and 20 kPa (135–150 mm Hg). After a 15-minute rest period, the stiffness of the superficial multifidus muscle will be measured in kPa using SWE.^[2]^

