#### 2.3.2. Control group.

The same procedure will be performed as in section 2.3.1., except that it will be conducted at 0 kPa (0 mm Hg).

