This RCT protocol has several limitations. First, it is not double-blinded, which may introduce researcher bias. However, the protocol minimizes bias by taking the mean of 10 out of the 12 quantitative values recorded in ultrasound images and excluding the maximum/minimum values. Second, it is not an absolute comparison study, and variance may be high owing to individual differences in values. However, it evaluates the effectiveness of recovery through a relative value comparison before and after treatment, and explores the significance of value changes with qualitative evaluations such as the NRS. Third, it is a placebo-controlled study, and information bias may be introduced if the patient understands the difference in treatment. However, it controls for participants’ expectations by excluding those who have experienced moving cupping, omitting treatment information, or offering a sham treatment similar to the actual procedure.

There are several areas that warrant further research to determine the full scope and implications of this treatment. Long-term research on the efficacy of moving cupping and SWE in treating CLBP may provide additional insight into the potential for relieving and preventing symptoms. Additionally, exploring the therapeutic efficacy of this combined therapy for other conditions may open up new avenues for treating other diseases. Moreover, studying the combined therapy of moving cupping and SWE with other treatments may help identify the most effective approach to managing pain and improving function. Finally, providing clinical guidelines for the application of the RCT results may help healthcare professionals use this therapy more effectively to benefit their patients.

In conclusion, we present a RCT protocol for investigating the efficacy and safety of moving cupping combined with SWE for patients with CLBP. This therapy may have a significant effect on pain reduction and functional improvement. Such research avenues can expand our understanding of the potential benefits of moving cupping and SWE, and help optimize their clinical application.

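### The listed exclusion covers only *medical* experience of moving cupping, while the blinding rationale requires no experience at all; the two wordings should be reconciled

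*Protocol article*

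**What the plan says.** The Protocol article states who may enter with respect to moving cupping in three places.

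- Section 2.2 (Study design and population) gives the rule and its purpose: "To ensure blinding, the study will include only patients with CLBP who have no prior experience with moving cupping".
- Section 2.2.3 (Exclusion criteria) lists as its first item "Individuals with medical experience of moving cupping".
- Section 3 (Discussion, limitations) accepts that "information bias may be introduced if the patient understands the difference in treatment" and answers this partly by "excluding those who have experienced moving cupping". It also mentions withholding treatment information and the similarity of the sham.

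Two other places bear on the point. Table 1 has the inclusion and exclusion criteria confirmed at screening. Sections 2.3.1 and 2.3.2 make suction the only stated difference between the arms: 18 to 20 kPa in the active arm and 0 kPa in the control arm, with the procedure otherwise the same.

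**The concern.** The section 2.2.3 criterion carries a qualifier, *medical*, that neither section 2.2 nor section 3 carries. Read literally, it is narrower than the rule on which the blinding argument depends. Someone who has had moving cupping at home or in another non-medical setting fails the section 2.2 rule but passes the listed criterion.

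This matters because the restriction exists to protect participant blinding. The limitations section already says the trial is not double-blinded, so what remains is largely the participants' own uncertainty about their arm. Section 2.2 treats experience of moving cupping as a threat to that uncertainty. If experienced patients enter, the threat the protocol set out to remove is back.

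The outcomes most exposed are those the patient reports: NRS, ODI, EQ-5D and PGA. The Introduction says that subjective reports of pain relief can be affected by placebo effects. The shear wave elastography reading is taken by a separate evaluator and depends less on what the patient believes.

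**Working it through.** No arithmetic in the plan is in question, so the check is a comparison of texts.

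**Step 1: the three wordings.**

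| Place | Who is kept out | Qualifier |
|---|---|---|
| Section 2.2 | anyone with prior experience of moving cupping | none |
| Section 2.2.3 | those with medical experience of moving cupping | *medical* |
| Section 3, limitations | anyone who has experienced moving cupping | none |

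**Step 2: where they disagree.** Take three kinds of patient.

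- No experience of moving cupping: eligible under all three texts.
- Experience in a medical setting: excluded under all three.
- Non-medical experience only: excluded under sections 2.2 and 3, but not under the literal wording of section 2.2.3.

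The conflict is confined to the third kind.

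**Step 3: does another listed criterion close the gap?** The five inclusion criteria in section 2.2.2 concern age, duration of low back pain, BMI, NRS score and consent. None mentions cupping. The other exclusions in section 2.2.3 do not mention it either. Table 1 directs screening to the inclusion and exclusion criteria, so a screener working only from the two lists would not meet the wider rule in section 2.2.

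**Step 4: does the article define the qualifier?** It does not. The next exclusion uses the same phrase for gold thread therapy, which suggests that it may be a loose way of saying that the person has received the treatment. The text does not settle this.

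**Step 5: can the size be worked out?** Let p be the fraction of randomised patients who enter only because of the narrower wording and who also recognise their arm. Let d be the shift that recognition causes in the between-arm difference on a self-reported scale. The distortion of the mean difference is then about p × d. The article gives no value for p or d and nothing from which to derive them. The only scale available is the sample size: 68 patients at 1:1 is 68 / 2 = 34 per arm, so each such patient would be 1 / 34 = 2.9% of an arm. How many there would be is unknown, and it may be none.

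**The case against.** The strongest reply is that section 2.2 is itself an eligibility rule, stated without qualification and with its purpose attached, and section 3 confirms it. Two of the three texts bar any experience, and nothing says that the list overrides section 2.2. On that view *medical experience* is loose wording and the intent is clear. Much of this stands. A reader might infer that patients with non-medical experience will be enrolled, but the article supports only that they could be, if screening follows the list to the letter. The reply does not remove the inconsistency, because the document still contains two rules and screening is tied to the criteria.

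A second reply is that the main threat to blinding is the sham, not this word. Patients who have never had cupping might also notice the absence of suction, and section 3 discloses the risk and names other protective measures. That is fair. A reader might infer that experienced patients will know their arm from the first session, or that correcting the criterion would secure blinding. The article establishes neither. Recognition of the sham is a plausible inference, and section 2.2 appears to rely on the same one, but it is not documented.

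Third, a reader might extend the point to stationary suction cupping, or to the lack of a question asking patients which treatment they think they received. Neither is part of the contradiction. All three texts concern moving cupping only, and a condensed article need not list every such item.

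**Conclusion.** The inconsistency is real and can be seen by reading sections 2.2, 2.2.3 and 3 together. The listed exclusion is narrower than the rule on which participant blinding is based, and a literal screener could admit patients with non-medical experience of moving cupping. This is a flaw in eligibility wording, minor to moderate in weight. It is worth correcting because it touches the one selection rule meant to protect blinding and costs almost nothing to mend.

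The conclusion assumes that *medical* is read in its ordinary sense. If it was meant to cover any past treatment, the flaw is one of expression only, and the correction is the same.

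No numerical effect can be claimed. A reader might assume a recognition rate and a shift in NRS and multiply them, but the article supports neither input. A general recognition rate would also count patients whose entry has nothing to do with this wording. Bias in favour of cupping is the direction one would expect, but it is not demonstrated. The concern applies mainly to NRS, ODI, EQ-5D and PGA, which Table 2 lists as secondary. Section 2.4 does not name the primary variable, though elastography is the evident reading.

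**What to change.** Reword the first exclusion in section 2.2.3 to match section 2.2, so that it covers any prior experience of moving cupping, medical or not, and use the same definition in section 3. This takes a few words; the downside is possibly a few more screen failures.

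Two additions are optional. First, record at screening any prior suction cupping of other kinds, so that a sensitivity analysis of the self-reported outcomes is possible; this costs one item in the medical history. Second, soften the statement in section 3 that participants' expectations are controlled, since the difference between 0 kPa and 18 to 20 kPa may be noticed even by patients with no experience of cupping. That costs one sentence.

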#### 2.2.4. Study protocol.

Table 1 presents the comprehensive study schedule. Each candidate will receive an explanation of the study protocol from a physician and is required to provide consent. Thereafter, they will be requested to sign an informed consent form before proceeding with the examination, as shown in Table 1. To allocate enrolled study participants to either the treatment or placebo group during visit 1, independent researchers will deliver sealed and opaque envelopes labeled consecutively with numbers, which have been randomly allocated by an independent statistician. The blinding will be maintained until submission of the paper. Before and after each treatment session, SWE will be conducted. Additionally, the physician will monitor the adverse events during each visit.

**Table 1 T1:** Study schedule.

		Treatment phase				Follow-up phase
		1 wk		2 wk		3 wk
	Screening	Visit 1	Visit 2	Visit 3	Visit 4	Visit 5
Informed consent acquisition	√					
Confirmation of eligibility (inclusion and exclusion criteria)	√					
Vital signs measurement	√	√	√	√	√	√
BMI measurement	√					
Demographic survey	√					
Medical history survey for the back and other organs	√					
Clinical examination†	√					
Physical examination	√					
Random allocation		√				
Moving cupping		√	√	√	√	
Placebo		√	√	√	√	
Outlier detection		√	√	√	√	
Confirmation of concomitant therapy		√	√	√	√	√
Shear wave elastography (before)		√	√	√	√	
Shear wave elastography (after)		√	√	√	√	
Numeric rating scale (NRS)	√	√			√	√
Oswestry disability index (ODI)		√			√	√
EQ-5D index		√			√	√
Patient global assessment (PGA)					√	√
Adverse event monitoring		√	√	√	√	√
Dropout confirmation		√	√	√	√	√

BMI = body mass index.

### 2.3. Intervention

#### 2.3.1. Moving cupping.

During the intervention, the participants will assume a prone position on a plinth with both elbows flexed to 90° and their shoulders abducted to 120° with external rotation. Cushions will be placed under the pelvis and legs to increase comfort, reduce lumbar lordosis, and optimize transducer contact, thereby enhancing the accuracy of the measurements obtained during the intervention.^[13]^ Thereafter, moving cupping will be administered bilaterally at the L1-5 level spinous process, 4 to 8 cm from the midline, for 5 minutes on each side, with pressure between 18 and 20 kPa (135–150 mm Hg). After a 15-minute rest period, the stiffness of the superficial multifidus muscle will be measured in kPa using SWE.^[2]^

#### 2.3.2. Control group.

The same procedure will be performed as in section 2.3.1., except that it will be conducted at 0 kPa (0 mm Hg).

#### 2.3.3. Shear-wave elastography measurement.

After measurement by the evaluator using ultrasound equipment, all SWE images will be stored on a separate storage device by a different researcher. To analyze the images, a Q-box will be inserted into the SWE image to evaluate the mean shear modulus in kPa of all the muscle fibers within the region of interest. The Q-box spatially averages the propagation speed of each shear wave to determine the shear modulus of each area of the imaged tissue. The shear modulus values will be averaged for the selected tissue area by averaging all the shear modulus values. Once the appropriate Q-box position is determined, the shear modulus values will be recorded 12 times in each trial. To reduce bias, the maximum and minimum values of the 12 recorded shear modulus (kPa) values will be excluded, and the average of the remaining 10 values recorded.

#### 2.3.4. Adverse events.

Possible adverse effects related to moving cupping include local adverse reactions such as blister formation, bleeding, persistent bruising, ongoing pain, stiffness, burning sensation, and heat at the treatment site. All significant adverse events that occur between the time of signing the informed consent form and the end of the trial will be documented in the medical records and reported to the Clinical Research Review Committee.

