### 2.5. Data collection and management

An electronically generated Case Report Form will be used and managed by qualified and authorized investigators and physicians. All the data recorded in the electronically generated Case Report Form will be consistent with those of the original material. During the study, the investigator will collect data at each visit. All study findings and records will be treated with strict confidentiality, and patients are to be identified solely by their patient number and/or birth date, and never by name. To protect participant anonymity, the investigator will maintain the confidentiality of the patient-identifying documents. The following data will be collected.

Date of birth (age), sex, medical history, history of current disease, and pregnancy status.Body weight and height at first visit, including BMI calculations.Vital signs (body temperature [°C], blood pressure [mm Hg], pulse rate [beats/minute]) at every visit.SWE before and after each treatment.NRS score at screening and visits 1, 4, and 5.Oswestry Disability Index and EQ-5D index at visits 1, 4, and 5.Patient Global Assessment at screening visits, and visits 1, 4, and 5.Outlier detection for each procedure.

Additionally, an independent clinical research organization will conduct data management and data monitoring. Interim analyses will not be conducted, and the trial will be terminated by the principal investigator when the study process for all enrolled study participants has been completed.

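### Adverse events are monitored at every visit without a severity limit, but the one documentation rule covers 'significant' events and the data list has no adverse-event item

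*Protocol article*

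**What the plan says.** Four parts of the protocol article bear on this point.

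- **Aim (2.2, Study design and population).** The opening sentence names both parts of the aim: "This study aims to investigate the efficacy and safety of moving cupping therapy for chronic pain using a parallel-arm RCT". The Discussion repeats the pairing of efficacy and safety.
- **Monitoring (2.2.4, Study protocol).** "Additionally, the physician will monitor the adverse events during each visit". In Table 1 the row "Adverse event monitoring" is ticked at visits 1 to 5. Neither the sentence nor the row sets a threshold of severity or importance.
- **Documentation (2.3.4, Adverse events).** The section first names the possible harms as "local adverse reactions such as blister formation, bleeding, persistent bruising, ongoing pain, stiffness, burning sensation, and heat at the treatment site". It then gives the rule: "All significant adverse events that occur between the time of signing the informed consent form and the end of the trial will be documented". The sentence goes on to say where these events go: "documented in the medical records and reported to the Clinical Research Review Committee".
- **Data collection (2.5, Data collection and management).** An itemised list follows the words "The following data will be collected". It covers demographics and history, body size, vital signs, shear wave elastography, the pain, disability, quality-of-life and global assessment scales, and outlier detection. Adverse events are not on it.

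**The concern.** A trial that sets out to assess safety needs its recording rule to be at least as wide as the harms it expects. The harms expected here are local skin and soft-tissue reactions, and many of these may be mild or moderate. The sentence that commits the trial to documenting adverse events is qualified by a word the article does not define. Nothing in the article says whether a small blister, a bruise or a burning sensation meets it.

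Two sites, or two physicians at one site, could follow the text faithfully and record different things. The count of treatment-site reactions by arm would then depend on individual judgement of what is significant, and would tend to be too low. A statement that the treatment was well tolerated would rest on data that may have been filtered before entry.

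**Working it through.** The article gives no figure for adverse events, so there is none to reproduce. The check follows one mild local reaction, noticed by the physician at a treatment visit, through the article's own text.

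1. **Is it looked for?** Yes. Section 2.2.4 and Table 1 put adverse-event monitoring at every treatment visit and at the follow-up visit, without a threshold.
2. **Must it be written down?** Not clearly. Section 2.3.4 contains the article's only commitment to document adverse events, and that commitment is worded for significant ones. The list of possible reactions comes just before it, but no sentence says that those reactions count as significant.
3. **Where would it be written down?** Section 2.3.4 names the medical records and the review committee. It does not name the case report form.
4. **Is it on the list of data collected?** No. Section 2.5 describes the electronic case report form and then itemises the data, with no adverse-event entry. The outlier detection item cannot stand in for one: Table 1 gives it a row separate from adverse-event monitoring, and Table 2 gives it an efficacy and psychological purpose.

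So the reaction is certain to be looked for but not certain to be recorded. Step 1 does not match steps 2 and 4.

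**Direction of the effect.** Let p1 and p0 be the true proportions of patients with a local reaction in the cupping and control arms, and let r be the share of those patients whose reaction is recorded, taken as equal in both arms. The recorded difference is r·p1 − r·p0 = r(p1 − p0). With r below 1, both proportions and the difference between them shrink. This needs no assumption that the arms are treated differently. None of p1, p0 or r is in the article, so the algebra gives the direction and no size.

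**Reach.** The elastography outcome and the patient-reported scales are collected under their own entries in Table 1 and section 2.5. The adverse-event rule does not touch them.

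**The case against.** The strongest reply is that the article does not say what a quick reading suggests. A reader might infer that non-significant events are deliberately excluded. The text does not support that: it promises to document all significant events and does not say that others are left out, and section 2.2.4 with Table 1 points the other way by scheduling unrestricted monitoring. The qualifier may also have been meant for reporting, since one sentence covers both the medical record and the committee. The listed reactions stand directly before the rule, are themselves called adverse reactions, and include persistent bruising and ongoing pain, which an author could well regard as significant. All of this stands. It makes the point an ambiguity to be reconciled, not a proven exclusion.

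A second reply is that this is a condensed article. The definition of the term, severity and causality grading, the case report form layout and a safety outcome row may all be in the full protocol or analysis plan. That also stands, so their absence, including the lack of a safety row in Table 2, is not part of the point. What remains is that three stated provisions do not fit together.

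Two further inferences should be resisted.

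- **Unequal filtering by arm.** The Discussion concedes that the trial is not double-blinded, so unequal filtering is possible. The article does not say whether the monitoring physician knows the allocation, so it is not shown.
- **A gap between consent and visit 1.** The documentation window opens at consent, while Table 1 starts monitoring at visit 1. Consent is taken at screening, so monitoring there would add almost nothing, and events before visit 1 precede any cupping.

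**Conclusion.** The point holds as a mismatch within the article. Safety is an aim and monitoring is unrestricted, but the only documentation rule is limited by an undefined word and doubles as a reporting rule, and the data list omits adverse events. Followed literally, the plan allows mild or moderate treatment-site reactions to go unrecorded, and the safety comparison would then be an under-count.

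This rests on one assumption: that those running the trial apply the sentence as written and judge some local reactions not to be significant. If the full protocol already requires every adverse event to be recorded, the consequence disappears and the wording of the article is all that needs correcting. No numerical size is claimed, because any figure would depend on an assumed reaction rate and an assumed degree of filtering. Efficacy conclusions are not affected.

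**What to change.** Reconcile sections 2.2.4, 2.3.4 and 2.5 as follows.

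- **2.3.4, recording.** State that all adverse events found by monitoring, of any severity and expressly including the treatment-site reactions already listed there, are recorded in the case report form in both arms and summarised by arm.
- **2.3.4, reporting.** Put committee reporting in a separate sentence. Keep 'significant' there as the reporting threshold and nowhere else, with its meaning stated or referenced.
- **2.5.** Add adverse events to the itemised data list, so that it matches the monitoring in section 2.2.4 and Table 1.

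The cost is a few lines of text, an adverse-event entry on the case report form if it lacks one, and a little more recording at visits already scheduled. No visit, procedure or patient is added.
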